### Sample Size Determination

This prospective trial will compare the onset, severity, and recovery of smell and taste loss as it relates to COVID-19 infection in a case-controlled prospective clinical trial. To perform our proposed cross-sectional analyses (see Statistical Analyses), we require a minimum sample size of 235 based on a power calculation of the sample size required to conduct a logistic regression. This sample will be used to analyze our primary outcome of whether loss of smell and taste acuity predict the likelihood of testing positive for COVID-19 infection. A sample size of 235 is required to observe an effect at 95% power (with a significance level of 0.05) using Pr(Y=1|X=1) H0=0.20 and an odds ratio of 1.723. This odds ratio was calculated as the smallest effect size of interest (SESOI) below which results would not be practically interesting. Given that it is difficult to draw well-informed sample size estimates from the current research, and that we instead opted to use the SESOI to calculate an estimated odds ratio and this minimum sample size, we will also conduct a sensitivity (posthoc) power analysis to demonstrate the effect sizes our final sample size is powered to detect.

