The majority of published studies investigating smell and taste loss related to COVID-19 have used subjective measurements of smell and taste, specifically self-report questionnaires. In Singapore, there have been anecdotal reports of smell and taste loss with COVID-19 infection [25,26], and in one prospective cohort of patients with COVID-19, it was found that 22.6% experienced acute olfactory loss [27]. The positive predictive value of acute olfactory loss for COVID-19 was 24.1%, and the negative predictive value was 96.5% [27]. Data collected to date have been based largely on self-report questionnaire measures, and there is a lack of objective data on measured smell and taste sensitivity. One study used a validated smell test, the University of Pennsylvania Smell Identification Test (UPSIT), to compare smell acuity in patients diagnosed with COVID-19 with a matched control group; it was shown that 98% of the patient group exhibited some smell dysfunction, scoring significantly lower on the UPSIT compared to controls [28].

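### The 95% power at 235 participants rests on an unexplained base rate of 0.20; at the 4.3% positivity implied by the one Singapore cohort cited with figures, power is about 56% one-sided or 44% two-sided

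*Protocol article*

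**What the plan says.** Under Sample Size Determination the article states "A sample size of 235 is required to observe an effect at 95% power", with alpha 0.05, "using Pr(Y=1|X=1) H0=0.20 and an odds ratio of 1.723". The outcome is a positive swab test and the predictor is loss of smell and taste acuity. The odds ratio is justified as the smallest effect of interest. No reason is given for 0.20, and neither the sidedness of the test nor the distribution of the predictor is stated. The section calls 235 a minimum, says that well-founded estimates are hard to draw from current research, and promises a post hoc sensitivity power analysis.

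The Introduction cites one Singapore cohort of COVID-19 patients with figures: "it was found that 22.6% experienced acute olfactory loss", followed by "The positive predictive value of acute olfactory loss for COVID-19 was 24.1%, and the negative predictive value was 96.5" per cent.

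Under Recruitment Procedure, people are approached after their screening swab. Under COVID-19 Diagnosis, the result is linked to their data afterwards. Study Design and Statistical Analysis call the study case-control, but give no case quota, case-to-control ratio or minimum number of cases.

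**The concern.** In a logistic regression the information comes mainly from the rarer outcome, here the swab-positives. Fixing the total at 235 delivers the stated power only if the positives arrive at about the assumed rate. That rate has no stated source, and the local figures cited in the same article point to one several times lower. Because people enter from screening regardless of swab result, the number of cases is left to chance.

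At stake are the test of association between sensory loss and infection, and the description of onset, severity and recovery among infected participants. If few test positive, both become imprecise, and the shortfall would be seen only after recruitment has closed.

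**Working it through.** **1. Reproducing 235.** Inputs from Sample Size Determination: base rate 0.20, odds ratio 1.723 (b = ln 1.723 = 0.544, b² = 0.296), power 95%, alpha 0.05. Assumption: the predictor is standard normal, so the odds ratio is per standard deviation. The Wald-test formula with variance correction (Demidenko) is

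n = (z_alpha·√V0 + z_power·√V1)² / b²

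V0 and V1 are the per-participant variances of the slope under the null and the alternative. With the intercept at logit(0.20), V0 = 5.96 and V1 = 6.89.

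- One-sided 0.05: (1.645·√5.96 + 1.645·√6.89)² / 0.296 = 234.6, which rounds up to 235.
- Two-sided 0.05: n = 280, and power at 235 is 91.2%.
- A binary predictor needs about 790 or more, so it does not give 235.

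The printed figure is therefore correct for a one-sided test with a continuous predictor and 0.20 as base rate.

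**2. Positivity implied by the cited cohort.** Inputs from the Introduction: loss among cases 22.6%, PPV 24.1%, NPV 96.5%. Assumption: all three come from one 2×2 table. Let t be the share with olfactory loss.

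- Positivity = 0.241t + 0.035(1 − t).
- Cases with loss: 0.241t = 0.226 × [0.241t + 0.035(1 − t)].
- Solution: t = 0.0407, positivity = 0.0434 (0.0428 to 0.0440 allowing for rounding of the inputs).

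**3. Expected positives among 235.**

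- At 20%: 235 × 0.20 = 47.
- At 4.34%: 235 × 0.0434 = 10.2, with a 95% binomial range of 5 to 17.
- Of these, 10.2 × 0.226 = 2.3 would have smell loss at the local rate, or 10.2 × 0.527 = 5.4 at the pooled prevalence that the Introduction also cites.

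**4. Power at 235 by positivity.** Same formula, odds ratio 1.723 per standard deviation:

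| Base rate | Expected positives | One-sided | Two-sided |
|---|---|---|---|
| 20% | 47 | 95% | 91% |
| 10% | 23.5 | 82% | 73% |
| 4.34% | 10.2 | 56% | 44% |

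If 4.34% is taken as the overall rate instead of the rate at the predictor's mean, the last row becomes 52% and 40%. The normal approximation is rough with about 10 events. Simulation of the Wald test gave 53% and 41% at 4.34%, and 94% and 90% at 20%, so the loss is not an artefact of the formula.

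**5. Size needed at 4.34%.** For 95% power: about 801 one-sided (801 × 0.0434 = 35 positives) or 960 two-sided (960 × 0.0434 = 42 positives).

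**The case against.** The strongest reply is that 4.3% is not this study's rate. It belongs to another cohort, it holds only if the three figures share one table, and recruitment here runs from July 2020 to March 2021. The article never labels 0.20 as swab positivity either; that reading follows from what the input means under the null. All of this stands, so the shortfall must be put conditionally. It does not supply a basis for 0.20.

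Second, 1.723 is the smallest effect of interest, and the true effect may be larger. The cohort's PPV and NPV imply an odds ratio of (0.241/0.759) / (0.035/0.965) = 8.8 for reported loss. Fisher-exact power (two-sided) at 235, with 4.34% positivity and 3.2% loss among negatives, is 96% if 52.7% of cases have loss, but 54% if 22.6% do. So the association test could still succeed at low positivity, but not with the local figure.

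Third, 235 is called a minimum and a sensitivity power analysis is promised. That is a fair concession by the authors. But no rule ties going beyond 235 to the number of cases, and a post hoc analysis reports a shortfall without preventing it.

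Three stronger readings are tempting and are not supported:

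- A reader might infer that the stated 95% drops to 44%. That pairs a one-sided start with a two-sided end; like for like it is 95% to 56%, or 91% to 44%.
- A reader might infer a calculation error. There is none, since 235 reproduces.
- A reader might infer that every primary aim fails. The comparison of the SSTT with household items and the factor analysis of the in-clinic test use all participants and are largely unaffected. Onset, duration and severity are planned as descriptive comparisons, so few cases would make them imprecise rather than impossible.

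**Conclusion.** The concern holds as a conditional one. The stated power depends on about 47 swab-positives. Neither the 0.20 behind that number nor the recruitment procedure supports it, and the only local figures cited point to about 10. At that rate power is roughly half what is needed to rely on the association test for the smallest effect of interest, and even at 10% positivity it is 82% one-sided or 73% two-sided.

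This rests on four assumptions: a standard normal predictor, 0.20 read as the base rate, one common table for the cohort figures, and positivity here somewhere between 4% and 20%. The first two are supported by the exact reproduction of 235; the last two cannot be checked from the article. It is a should-fix point about an unsupported planning assumption.

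**What to change.** 1. State whether the test is one- or two-sided, and that the odds ratio is per standard deviation of the predictor if that is what was used.
2. Replace the single power figure with a table over 4% to 20% positivity, and state that the 95% at 235 rests on about 47 positives.
3. Count swab-positives among those already recruited (69 by October 2, 2020) without looking at smell or taste data, and report power at that rate while recruitment is open, not only post hoc. The count is informative: 69 × 0.20 = 13.8 expected at 20%, against 69 × 0.0434 = 3.0 at 4.34%.
4. Fit the primary logistic model with Firth penalisation and profile-likelihood intervals, so that estimates remain usable if positives are few.

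The cost is one table, one or two sentences, a count from results that the study has consent to access, and a change of estimation routine. The stated power will look less favourable. These steps do not themselves add cases; they show whether more are needed while there is still time to decide.

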### Primary Outcomes

The primary outcomes are (1) to measure the onset, severity, duration, and recovery of changes to smell and taste sensitivity resulting from COVID-19 infection and (2) to assess the efficacy of the SSTT as a simple diagnostic approach. Data will be used to test the association of smell and taste loss with positive COVID-19 infection, measuring changes in sensory acuity from baseline (initial screening, Day 0) to the end of the 4-week monitoring period, to investigate the best predictors of recovery of smell and taste sensitivity. In addition, the primary methodological outcome is a comparison of the consistency and discriminability of self-assessment standardized home use tests compared to both the common household items home use test and the questionnaire-based measures. The findings will inform best practice approaches for future self-assessment of smell and taste acuity among people with suspected COVID-19 infection. This will be measured directly via responses to the daily home-use smell and taste test, complemented by measures from the self-reported questionnaire responses (SSTQ, SNOT-22, GCCRQ).

### Secondary Outcomes

The secondary outcomes will include assessment of experienced symptoms and changes in appetite and food-related quality of life over the duration of smell and taste loss and the 4-week follow-up period. This will be assessed via the home-use test questionnaires.

### Statistical Analysis

Using a case-control study design for people testing positive (case) or negative (control) for COVID-19 infection, data will be collected on changes in smell and taste loss that have occurred in the 2 weeks prior to the COVID-19 test and on smell and taste acuity changes measured on a daily basis for up to 28 days following the COVID-19 test. The data will be used for descriptive comparisons of the onset, duration, and severity of smell and taste changes with COVID-19 infection and to report on the incidence of these changes among participants testing positive for COVID-19 infection (and those recovering from infection).

Logistic regression analysis will be used to estimate the odds ratio for loss of smell and taste sensitivity as a predictor of testing positive for COVID-19 infection. This will also enable comparison of smell and taste loss as a predictor of COVID-19 infection compared to other symptoms, such as fever and dry cough. Pearson correlations will be used to investigate relationships between smell and taste changes and other symptoms. Time-series analysis of variance (ANOVA) models will be run to investigate temporal changes in smell and taste ratings over time, with baseline ratings in smell and taste acuity corrected for at an individual level. Linear mixed models will be used to test for significant differences in smell and taste acuity between groups, with participants stratified by their COVID-19 infection status.

Factor analyses, using oblique rotation and baseline home-use test responses (conducted in-clinic), will be conducted to assess the internal consistency of our smell and taste test. Adjusted odds ratios will be calculated to investigate the best predictors of recovery of smell and taste acuity postinfection. Linear regression will be run to examine whether responses to the smell and taste test predict responses to the household item odor test (smell) and self-reported taste acuity, respectively. Regression analyses will be conducted to investigate the association between loss of smell and taste acuity and self-reported appetite and food-related quality of life. All statistical analyses will be completed using SPSS (IBM Corporation).

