**Assessments**								
	Baseline variables: gender, age, education status, nationality, ethnicity, employment status, smoking status, vaping status, medication, COVID-19 test result		✓					
	Primary outcome variables: COVID-19 symptoms (and onset), smell and taste acuity			✓	✓	✓	✓	✓
	Secondary outcome variables: appetite, food enjoyment, eating behaviors, nausea, weight, food-related quality of life		✓	✓	✓	✓	✓	✓

^a^SSTT: Singapore Smell and Taste Test.

^b^Participants were asked to complete the SSTT daily from Day 1 to Day 28.

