### Measures

On the day of their COVID-19 swab test (Day 0), after consenting to participate in the trial, participants will complete three questionnaires to document recent changes in their smell, taste, and chemesthetic ability and to detail the frequency of a wide range of nasopharyngeal symptoms. These questionnaires include the Singapore Smell and Taste Questionnaire (SSTQ, Multimedia Appendix 1), the 22-item Sino-Nasal Outcome Test (SNOT-22) [34], and the recently developed Global Consortium for Chemosensory Research questionnaire (GCCRQ) [12]. Participants will receive the Singapore Smell and Taste Test (SSTT, Multimedia Appendix 2), a standardized home use testing kit to monitor their smell and taste acuity, and will be given a demonstration of the self-assessment procedure that they will complete daily at their place of residence for the following 28 days. All the questionnaires and instructions are available in English, Mandarin, Tamil, and Bengali, and the participants will complete all the measures via Compusense Cloud web-based data acquisition software (Compusense Inc).

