### The SSTQ

Participants will complete the SSTQ (Multimedia Appendix 1) to record any recent changes in smell and taste and to describe the occurrence of sino-nasal or other COVID-19 symptoms. Participants will rate their current smell and taste sensitivity using the SSTQ (Day 0) to provide a baseline measure for their smell and taste sensitivity. This initial self-report questionnaire will quantify any recent changes in smell and taste acuity and includes questions on the participants’ basic demographics, the COVID-19–related symptoms they have experienced, the temporal onset of these symptoms, the smell and taste acuity of the participants, and their appetite-related quality of life (eg, enjoyment of food). See Multimedia Appendix 3 for information on the sources of the questionnaire items.

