### Daily Smell and Taste Testing

The study participants’ smell and taste acuity will be prospectively measured for up to 28 days following their clinic visit for COVID-19 testing using the home-based assessment tools detailed in this section. At the start of each daily test session, participants are to report on any changes in their smell and taste acuity by selecting either “improved,” “stayed the same,” or “worsened” before rating their current sense of smell and taste from “no sense of [smell/taste] at all” to “extremely strong sense of [smell/taste].” Participants will also be asked to “check all that apply” across a list of symptoms they have experienced in the last 24 hours from a list of COVID-19–relevant symptoms.

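### The temporal models have no time index except days since the swab, so within cases the mean curve mixes stages of illness and can understate peak loss; an onset-aligned analysis should be added

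*Protocol article*

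**What the plan says.** The second primary objective (Introduction) and the first primary outcome concern the onset, severity and recovery of smell and taste changes. For the course over time, the Statistical Analysis section states that "Time-series analysis of variance (ANOVA) models will be run to investigate temporal changes in smell and taste ratings over time". It adds that this is to be done "with baseline ratings in smell and taste acuity corrected for at an individual level". For differences by infection status, mixed models are planned. The same section also plans descriptive comparisons of onset, duration and severity, and adjusted odds ratios for predictors of recovery.

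The time indices in the article are these:

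- Measures: the first assessment is "On the day of their COVID-19 swab test (Day 0), after consenting to participate in the trial".
- Table 1, footnote b: "Participants were asked to complete the SSTT daily from Day 1 to Day 28".
- Daily Smell and Taste Testing: acuity is "prospectively measured for up to 28 days following their clinic visit for COVID-19 testing".
- Primary Outcomes: "measuring changes in sensory acuity from baseline (initial screening, Day 0) to the end of the 4-week monitoring period".

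Two passages bear on each person's stage of illness. Under Statistical Analysis, "data will be collected on changes in smell and taste loss that have occurred in the 2 weeks prior to the COVID-19 test". Under The SSTQ, the Day 0 questionnaire covers COVID-19-related symptoms and "the temporal onset of these symptoms", and its rating of current smell and taste serves as the baseline.

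**The concern.** The swab day marks when a person came for testing. It is not a fixed point in the illness. Loss may have begun up to two weeks earlier or may begin during follow-up, and the study means to capture both. On any given study day the cases are therefore a mixture of people before onset, at their worst and recovering. The Introduction describes the loss as often abrupt. Averaging abrupt losses that start on different days gives a shallower, more gradual curve, whose shape depends partly on how promptly people presented.

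The baseline adds to this. For anyone already affected, the Day 0 rating is not a pre-illness value, so change from it leaves out the loss that has already happened. At stake is whether the modelled curve can speak to severity and recovery, which belong to a primary objective.

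**Working it through.** **No planned figure to reproduce.** The article gives no number for the temporal models. Its sample size of 235 concerns the logistic regression and plays no part here.

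**Direction.** On any study day, the mean loss over cases is at most the mean of their individual maximum losses. The peak of the mean curve therefore cannot exceed the mean individual peak. The two are equal only if all cases are at their maximum on a common day.

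**Size (illustrative).** The documents give neither the shape of the loss nor the spread of onset, so everything in this step is assumed. Each case loses 60 points on the visual analog scale (VAS): a linear fall over 1 day, a plateau of *p* days, then linear recovery over *r* days. Call the loss *t* days after onset *f(t)*. Onset is uniform from *a* days before to *b* days after the swab. The mean loss on study day *d* is then

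mean(d) = [area under *f* from *t* = d − b to *t* = d + a] / (a + b).

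Worked cases for *a* = 14, *b* = 3 (width 17 days):

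- *p* = 3, *r* = 5: the whole curve (9 days) fits in the window. Area = 60 × (0.5 + 3 + 2.5) = 360; 360/17 = 21.2.
- *p* = 5, *r* = 10: the whole curve (16 days) fits. Area = 60 × (0.5 + 5 + 5) = 630; 630/17 = 37.1.
- *p* = 10, *r* = 14, day 4: *t* runs from 1 to 18. Plateau 10 × 60 = 600; recovery falls from 60 to 30 over 7 days, 45 × 7 = 315; 915/17 = 53.8.

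The same formula gives these peaks of the mean curve on the swab clock. The true peak is 60 throughout.

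| Onset relative to swab | p 3, r 5 | p 5, r 10 | p 10, r 14 |
|---|---|---|---|
| −3 to +3 days | 51.0 | 59.5 | 60.0 |
| −7 to +3 days | 36.0 | 52.5 | 60.0 |
| −14 to +3 days | 21.2 | 37.1 | 53.8 |

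Counted from true onset, the peak is 60 in every cell. A simulation of the same scenarios agrees to within 0.5 points.

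**Effect of the baseline.** If the correction means subtracting the Day 0 rating (the article does not say how it is done), the largest mean further decline is the peak minus the Day 0 mean. For onset −14 to +3 days:

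- *p* = 3, *r* = 5: Day 0 mean 360/17 = 21.2; further decline 0.
- *p* = 5, *r* = 10: Day 0 mean (30 + 300 + 288)/17 = 36.4; further decline 0.7.
- *p* = 10, *r* = 14: Day 0 mean (30 + 600 + 160.7)/17 = 46.5; further decline 7.3.

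The share already affected on Day 0 is 9/17 = 53%, 14/17 = 82% and 14/17 = 82%. The change curve then shows almost only recovery. With onset within ±3 days the further decline is 26 to 35 points: Day 0 mean 150/6 = 25, subtracted from 51.0, 59.5 and 60.0.

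**Recall error on the onset clock.** The formula also covers an error in the recalled date. With a uniform error of ±2 days and *p* = 3, *r* = 5, *t* runs from 1 to 5 at best: (3 × 60 + 54)/4 = 58.5. For the two longer curves the peak stays at 60. An error of ±3 days is the first row of the table.

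**The case against.** **The clock is inferred.** The sentence on the ANOVA names no time origin, and the Day 0 wording under Primary Outcomes concerns change from baseline to week 4 and predictors of recovery. This is a condensed article, and detail of this kind often sits in a fuller document. That stands: a reader might infer that the plan expressly fixes swab day as the model's time scale, and it does not. Still, swab day is the only index given, and baseline is set at Day 0 under both The SSTQ and Primary Outcomes.

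**Onset is not ignored.** A reader might also infer that onset data go unused, or that the primary outcomes as a whole are distorted. The text does not support either reading. Onset, duration and severity get descriptive comparisons, recovery gets adjusted odds ratios, and nothing says that peak severity will be read from a group mean curve.

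**The dates may be incomplete.** The SSTQ section ties onset to symptoms and lists smell and taste acuity separately. The questionnaire itself is not shown, so a dated onset of smell or taste loss before the swab is not assured. That stands and limits the remedy.

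**Onset alignment has its own selection.** Cases affected before Day 0 have no test ratings from their first days of loss. The early part of an onset-aligned curve rests on prompt presenters and on those whose loss began during follow-up. If depth of loss is related to promptness, that curve also depends on presentation. This stands as a stated limitation. It argues for adding the analysis, not for replacing the study-day model.

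**Controls have no onset.** Study day is the one clock that both groups share, and change after presenting for testing is a fair question for this design. The case-control contrast should stay on it.

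**Conclusion.** The point holds in a limited form. On the only clock the article offers, with a Day 0 baseline, a mean curve among cases mixes stages of illness. It can understate peak loss and can show mainly recovery. The bound on the peak is arithmetic and needs no assumption.

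The size rests wholly on assumed curves and onset spreads. It runs from nothing (60 of 60, long plateau and onset within 3 to 10 days' width) to about two thirds of the peak (21 of 60, short plateau and onset spread over 17 days). The documents do not show where this study falls, so a claim that severity will be halved, or understated by any given amount, is not supported. The baseline result further assumes that the correction is a change from Day 0.

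The descriptive comparisons partly serve the same objective but do not realign the model. This is a worthwhile addition for the second primary objective; it does not invalidate the plan.

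**What to change.** State the time scale of each temporal model. Keep study day, with the Day 0 baseline, for the case-control contrast. Add a within-case mixed model on days since onset of smell or taste loss, with each case entering at their own time since onset. Take onset from the SSTQ where it gives a date, and otherwise from the first affected day in the daily ratings. Report nadir and recovery slope from this model, with the number of cases contributing at each day since onset.

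The cost is analysis text, with no new visits and no change to the sample size, because the data are largely already collected. The downsides should be stated in the plan:

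- Recalled onset is imprecise by a day or more.
- Early post-onset days rest on prompt presenters and on onsets during follow-up.
- Cases without an onset date stay in the study-day analysis only.

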**Conclusions:**

To our knowledge, this study will be the first to collect longitudinal data on changes to smell and taste sensitivity related to clinically diagnosed COVID-19 infection, confirmed by PCR swab test, in a population-based cohort. The findings will provide temporal insights on the onset, severity, and recovery of sensory changes with COVID-19 infection, the consistency of symptoms, and the frequency of full smell recovery among patients with COVID-19. This self-administered and cost-effective approach has many advantages over self-report questionnaire–based methods and provides a more objective measure of smell and taste changes associated with COVID-19 infection; this will encourage otherwise asymptomatic individuals who are potential spreaders of the virus to self-isolate and seek formal medical diagnosis if they experience a sudden change in sensory acuity. This broadened case finding can potentially help control the COVID-19 pandemic and reduce the emergence of clusters of infections.

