In addition, to our knowledge, no longitudinal study has yet been performed to systematically track the onset, severity, and recovery of changes to sensory acuity across the preinfection and postinfection periods of COVID-19, with emerging reports of sustained anosmia among a small proportion of people who have recovered from infection. To date, questionnaire measures alone have been published; these studies relied on self-reporting and may not accurately reflect the true extent of smell and taste changes during COVID-19 infection in the absence of a standardized tool for such measurements. Reliance on self-report questionnaire data and variable approaches could help explain the wide variability in the reported prevalence of olfactory dysfunction with COVID-19 infection (5%-98%) [29]. Therefore, there is a need for objective testing of smell and taste loss in patients infected with COVID-19 using standardized smell and taste stimuli [29-31]. Moreover, due to extensive restrictions on movement, the need to socially distance, and the potential for infection spread with reusable standardized odor and taste test materials, the collection of in-person physical data is challenging. Furthermore, although clinically validated smell and taste assessments are preferred, they are often expensive, and their reuse is not recommended among infected patient populations. Home use sensory tests have been developed to track changes in smell and taste sensitivity using common household items as test stimuli [32,33]. However, these tests rely on participants sourcing and preparing their own test stimuli from available household items; this introduces unwanted stimulus variation, which may present problems for comparability of smell loss across individuals using different stimuli.

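### Duration and recovery are analysed by description and odds ratios, although observation stops 28 days after the swab and covers unequal time since onset

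*Protocol article*

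**What the plan says.** The Primary Outcomes section of the protocol article sets as its first aim "to measure the onset, severity, duration, and recovery of changes to smell and taste sensitivity resulting from COVID-19 infection". The abstract's conclusions also promise "the frequency of full smell recovery among patients with COVID-19".

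The Statistical Analysis section names two tools for these quantities. For duration: "The data will be used for descriptive comparisons of the onset, duration, and severity of smell and taste changes with COVID-19 infection". For recovery: "Adjusted odds ratios will be calculated to investigate the best predictors of recovery of smell and taste acuity postinfection". Time-series ANOVA and linear mixed models are planned as well, but for the ratings over time and for group differences in acuity.

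The observation window has two parts: a recalled part, "changes in smell and taste loss that have occurred in the 2 weeks prior to the COVID-19 test", and a measured part, "smell and taste acuity changes measured on a daily basis for up to 28 days following the COVID-19 test". On Day 0 the SSTQ asks about COVID-19-related symptoms and "the temporal onset of these symptoms".

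The Introduction cites reports of "sustained anosmia among a small proportion of people who have recovered from infection", and the hypothesis expects return of function in the majority, not in everyone. Under Data Management, people with fewer than 25% of tests leave the longitudinal analyses of the home-use procedure, and a missing value removes a person listwise from the analysis concerned.

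**The concern.** Duration and recovery are times to an event, and the two named methods have no place for an event not yet seen or for unequal time in which to see it.

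- **Right-censoring.** A loss still present at Day 28, or at a person's last completed test, has a known minimum length but no observed duration. By the protocol's own account some losses will be like this.
- **Unequal clock.** Day 0 is the day of the swab, not of onset. Two people with the same status on Day 28 may have had quite different times in which to recover.
- **Early stopping.** Someone who stops testing while still impaired contributes real information. If the analysis needs a later status, the listwise rule discards that person entirely.

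At stake are the duration estimate, the recovered fraction and the list of best predictors of recovery. Any characteristic linked to being swabbed early or late could appear to predict recovery.

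**Working it through.** The plan states no figure for duration or recovery. Its only computed figure, the sample size of 235, concerns the logistic regression of the swab result and has no bearing here. The sizes below therefore rest on assumptions.

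**Inputs from the article.** End of observation: 28 days after the swab. Look-back: 14 days.

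**Assumptions.** True median duration M = 7, 14 or 28 days. Durations are exponential, so S(t) = 2^(-t/M) and mean m = M/ln 2 = 10.1, 20.2 or 40.4 days. Onset is u days before the swab, u uniform on 0-14. A lognormal with log-SD 1 serves as a second shape.

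**1. Observation time from onset.** 28 + u, at most 28 + 14 = 42 days; for onset v days after the swab, 28 - v, below 28 days.

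**2. Mean duration over all losses, ongoing ones cut at Day 28.** Fraction unrecovered: q = 2^(-28/M) × (1 - 2^(-14/M)) / (14 ln 2 / M). For an exponential, the cut mean is m(1 - q).

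| M | q | cut mean | true mean | ratio |
|---|---|---|---|---|
| 7 | 0.0625 × 0.75/1.386 = 0.034 | 9.8 | 10.1 | 97% |
| 14 | 0.25 × 0.5/0.693 = 0.180 | 16.6 | 20.2 | 82% |
| 28 | 0.5 × 0.293/0.347 = 0.423 | 23.3 | 40.4 | 58% |

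The lognormal shape gives about 89%, 74% and 53% by simulation.

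**3. The same summary in people still impaired on Day 0, dated from onset.** Longer losses are more likely to be present at the swab. The mean is ū + m(1 - 2^(-28/M)), with ū = m - 14 × 2^(-14/M)/(1 - 2^(-14/M)).

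- M = 7: 5.4 + 9.5 = 14.9 against 10.1 (overstated)
- M = 14: 6.2 + 15.15 = about 21.4 against 20.2 (slightly overstated)
- M = 28: 6.6 + 20.2 = 26.8 against 40.4 (understated)

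The simulated lognormal gives 15.0 against 11.6, 20.7 against 23.1 and 26.3 against 46.2, so at M = 14 even the sign depends on the shape.

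**4. Recovered by Day 28, early onset (u = 10-14) against late onset (u = 0-4), all losses.** Recovered = 1 - average of S(28 + u) over each range.

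- M = 7: 98.08% against 94.84%; odds ratio (0.9808/0.0192)/(0.9484/0.0516) = 2.8
- M = 14: 86.18% against 77.32%; (0.8618/0.1382)/(0.7732/0.2268) = 1.8
- M = 28: 62.83% against 52.40%; (0.6283/0.3717)/(0.5240/0.4760) = 1.5

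Nothing but onset timing differs between the groups. The lognormal gives 95.9% against 92.7%, 85.3% against 77.7% and 63.9% against 52.7%, that is about 1.85, 1.7 and 1.6.

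**5. How far step 4 depends on who is analysed.** It counts losses that resolved before the swab. Among people impaired on Day 0, the exponential gives 1 - 2^(-28/M) whatever the onset date, so the odds ratio is 1. The lognormal, using 1 - average S(28 + u)/average S(u), gives 86.3% against 91.7%, 73.9% against 76.8% and 55.0% against 52.4%: odds ratios 0.57, 0.85 and 1.11. Onset 0-14 days after the swab brings the distortion back. Under the exponential, 86.5%, 63.9% and 40.2% of these recover in the window, against 93.75%, 75% and 50% of those impaired on Day 0: odds ratios of about 2.3, 1.7 and 1.5.

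**6. Check of the remedy.** In simulated exponential data (200,000 losses, quarter-day grid), Kaplan-Meier from onset returns medians of 7.0, 14.3 and 28.3 days. With delayed entry, using only people impaired on Day 0, it returns 7.3, 14.8 and 28.5.

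**The case against.** The strongest reply is that the article is condensed and its wording leaves room. A descriptive comparison could include a Kaplan-Meier median; nothing confines duration to people who recovered. The odds ratios are adjusted, the covariates are not listed, and recorded onset could be one of them. A discrete-time logistic model also yields adjusted odds ratios. The definition of recovery and the covariate list may stand in a fuller document, and the mixed models already follow ratings over 28 days.

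Much of this is fair. A reader might infer that durations will simply be understated; the article does not support that, because it names no estimator and the direction reverses in people already impaired on Day 0. A reader might also infer that recovery status is misclassified. That is not shown either: someone unrecovered on Day 28 is correctly recorded as such, and an early stopper lacking a needed value is removed, which is a matter of selection. Nor does the article say that the 25% rule governs the recovery analysis.

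What the reply does not remove is that the article chose methods for a primary outcome, and neither, as named, handles censoring or time since onset. Models of ratings estimate neither a duration nor a probability of recovery. The listwise rule is explicit and conflicts with using incomplete follow-up.

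**Conclusion.** The point holds as a mismatch between stated methods and data structure. Duration summaries will be biased, but the direction depends on the unknown duration distribution and on whether losses present on Day 0 are dated from onset. Over all losses with onset in the look-back window, the cut mean is 97% to 58% of the truth for assumed exponential medians of 7 to 28 days. The bias is small if losses are short. The hypothesis that most people recover makes the longest scenario less likely, though the article gives no distribution.

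A recovered yes/no odds ratio mixes predictors with time since onset unless that is handled: about 2.8 to 1.5 over all such losses, but 1 or even reversed if only people impaired on Day 0 are compared. These figures illustrate; they do not predict the trial's results. The plan should be changed before analysis, and nothing in the design prevents it.

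**What to change.** - **Event and clock.** Define recovery, including the reference level for people already impaired on Day 0. Analyse time from reported onset of loss (SSTQ, or the daily test for onset after the swab) to recovery.
- **Censoring.** Censor at the last completed test in place of listwise deletion for these analyses.
- **Entry.** Use delayed entry at Day 0 for people still impaired at the swab. Report losses that resolved earlier separately, or include them from onset if a recovery date was recorded.
- **Estimates.** Give Kaplan-Meier medians and recovery probabilities at fixed times since onset, such as 7, 14, 21 and 28 days, with confidence intervals.
- **Predictors.** Fit a Cox or discrete-time model on the same clock. The discrete-time model is a logistic regression on person-days, counted from Day 0 for those already impaired, so adjusted odds ratios can stay.
- **Sensitivity.** Repeat with time from Day 0.

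The cost is analysis wording: daily tests and symptom onset are already collected, assuming the SSTQ onset item covers smell and taste loss (its appendix is not shown). The small downside is reliance on recalled onset dates and on censoring unrelated to recovery.
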